### Sample size

2.4

We used EpiCalc 2000 for sample size estimation, set significance = 0.05, power = 80%, ratio of cases to controls = 1, risk ratio to detect = 2, proportion (%) controls exposed = 15% (4.4%–24.5%). The sample size was 207 in each of the observation group and the control group.

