### Data analysis

3.7

Statistical analyses will be conducted with SPSS version 20.0 software (SPSS, Chicago, IL). Statistical differences between the 2 groups will be tested using Student *t* test for normally distributed variables or Fisher exact test for dichotomous variables. Two-tailed *P* values < .05 will be considered statistically significant.

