## Discussion

4

NBP is a neuroprotective drug extracted from celery seeds. Its active ingredient is dl-3-NBP, which can increase the levels of nitric oxide and prostacyclin in the brain vascular endothelium, reduce the intracellular calcium ion concentration, inhibit glutamate release, reduce the content of arachidonic acid, inhibit oxygen free radicals, increase the activity of antioxidant enzymes and other mechanisms for multiple pathological links of cerebral ischemic. Ischemic stroke will develop neurological deficits in the acute phase. Neuroprotective drugs can reduce ischemic injury through various ways and improve the functional prognosis of patients. It can be used as an effective auxiliary method for the treatment of patients with ischemic stroke during the acute phase. Our study will evaluate the safety of NBP in AIS patients. If the research proves that NBP can reduce the new CMBs of AIS, it will provide new evidence for the treatment of NBP in AIS; if the research finds that NBP will not affect the new CMBs, it will confirm the safety of NBP; and if the study finds that NBP will increase the new CMBs, it will remind clinicians to carefully evaluate treatment options for patients at greater risk of bleeding.

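### A finding of no effect on new CMBs is to be read as confirming the safety of NBP, but a test of difference with 207 per arm cannot show that

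*Protocol article*

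**What the plan says.** Section 2.1 of the protocol article makes new CMBs the indicator by which the safety of NBP is judged, and section 3.4 makes the effect of NBP on new CMBs the primary outcome.

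The Discussion (section 4) sets out three possible results and a reading for each: a reduction, no effect, or an increase. For the middle one it says: "if the research finds that NBP will not affect the new CMBs, it will confirm the safety of NBP".

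Section 3.7 gives the only decision criterion. For binary outcomes it names the "Fisher exact test for dichotomous variables", and it adds: "Two-tailed *P* values < .05 will be considered statistically significant".

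Section 2.4 sizes the trial with "set significance = 0.05, power = 80%, ratio of cases to controls = 1", "risk ratio to detect = 2" and "proportion (%) controls exposed = 15% (4.4%–24.5%)", and arrives at 207 per group.

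**The concern.** A test of no difference can give evidence of a difference. Failing to reject does not show that a harmful difference is absent; the result may only mean that the trial was too imprecise to see one. The Discussion nevertheless attaches a positive safety claim to the null branch.

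This matters more here than in an efficacy trial. Safety is the declared aim, and the Introduction itself gives a mechanism by which NBP could increase new CMBs (an aspirin-like effect on platelets). A clinically unwelcome increase that the trial misses would be reported to clinicians as confirmed safety, when the data might be compatible with a substantial excess of microbleeds.

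**Working it through.** **Inputs.** N = 207 per arm, control rate 15% (quoted range 4.4% to 24.5%), effect to detect 2, two-sided 5%, power 80% (section 2.4); Fisher exact test (section 3.7). The true risk ratio of 1.5 is my illustration, not a figure from the plan. All calculations take 207 per arm as evaluable.

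**1. The plan's own N.** Per arm, n = [1.96·√(2p̄(1−p̄)) + 0.8416·√(p₀(1−p₀) + p₁(1−p₁))]² / (p₁−p₀)², where p̄ is the mean of p₀ and p₁.
- Effect 2 read as a risk ratio, 15% vs 30%: n = 120.5, so 121. This does not reproduce 207.
- Effect 2 read as an odds ratio, p₁ = 2 × 0.15/(1 + 0.15) = 26.1%: n = 207.3. This reproduces 207 (208 if rounded up).

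The N therefore fits an odds ratio of 2, which at 15% is a risk ratio of 0.261/0.15 = 1.74. The steps below use N = 207 directly, so they do not depend on how it was reached.

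**2. Chance of a non-significant result when harm is real.** Exact power of the two-sided Fisher test, by summing over all pairs of counts with 207 per arm, for a true risk ratio of 1.5:

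| Control rate | NBP rate | Power | Non-significant |
|---|---|---|---|
| 4.4% | 6.6% | 12% | 88% |
| 10% | 15% | 29% | 71% |
| 15% | 22.5% | 45% | 55% |
| 20% | 30% | 61% | 39% |
| 24.5% | 36.75% | 74% | 26% |

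The non-significant share falls to 50% at a control rate of about 16.5%. At 15% the normal approximation gives 50.2% in place of 54.8%.

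**3. What a null result leaves open.** SE(log RR) = √(1/x₁ − 1/207 + 1/x₀ − 1/207).
- 31 vs 31 events (15.0% each): SE = √(2/31 − 2/207) = 0.234. The 95% CI is exp(±1.96 × 0.234) = 0.63 to 1.58. With exactly equal observed rates, a 50% increase is not excluded.
- 46 vs 31 events (22.2% vs 15.0%): RR = 46/31 = 1.48, SE = 0.211, 95% CI 0.98 to 2.24, Fisher P = 0.077. This result is non-significant, and its interval includes a doubling.

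**4. What 207 per arm can exclude.** Probability that the upper 95% limit for the risk ratio falls below a margin, control rate 15%, by the same summation:
- True RR 1, margin 2: about 83%. The normal approximation gives Φ(0.693/0.234 − 1.96) = 84%.
- True RR 1, margin 1.5: about 41%.
- True RR 1.5, margin 2: about 28%.

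The first figure also moves with the control rate: about 65% at 10% and about 33% at 4.4%.

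**The case against.** **The rule is inferred.** The Discussion speaks of finding no effect; it does not mention P > .05, and nothing in the text links it to section 3.7. A reader might say that the protocol defines non-significance as safety, and in those words it does not. The inference stands, because section 3.7 offers no other criterion by which the trial could find that there is no effect.

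**Margins and intervals may be left to the analysis plan.** This is fair, and the silence of a condensed article on confidence intervals is not the defect. The defect is an inference that the article does state and that its design does not support.

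**The trial is better against a doubling than it looks.** This also stands. At 15% vs 30%, Fisher power with 207 per arm is about 95%, because N matches an odds ratio of 2. The weakness lies in smaller increases and in low control rates; at 4.4% a true doubling would be missed about 63% of the time.

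**Stronger readings that the document does not support.**
- That a 50% increase would more often than not pass as safe, whatever the control rate. This holds at 15% but fails above about 16.5%, well inside the quoted range.
- That a non-significant result is the likeliest outcome. The Introduction says that the direction of effect cannot be predicted.
- That missing scans must push towards a finding of safety. Fewer scans lower power, but differential loss could bias the comparison either way.

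**It is one sentence and can be corrected at reporting.** True, but it is the article's only statement of how a null primary result will be interpreted, and a rule chosen after the data are known is worth much less.

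**Conclusion.** The point holds. The article commits in advance to reading a finding of no effect as confirmed safety, and a two-sided test of difference at this size cannot bear that reading. At the planning rate of 15% with 207 evaluable per arm, a true risk ratio of 1.5 would be non-significant in about 55% of trials; across the quoted control rates the figure runs from about 88% (4.4%) to about 26% (24.5%). The logical error is present at every rate, and only its size changes.

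The conclusion rests on two assumptions: that finding no effect means a non-significant test, which is an inference from section 3.7, and that a 50% increase would matter, which is my illustration. The document sets no threshold for a material increase.

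**What to change.** Replace the null-result sentence in the Discussion and add to section 3.7 that:
- the risk ratio and risk difference for new CMBs will be reported with 95% confidence intervals;
- no material increase will be concluded only if the upper 95% limit lies below a margin that is justified and fixed before any outcome data are seen (the trial is single-blind, so a reference to unblinding would be a loose anchor);
- otherwise a non-significant result will be called inconclusive.

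State also what 207 evaluable per arm can exclude at a 15% control rate and a true risk ratio of 1: about 83% power for an upper limit below 2 and about 41% for one below 1.5. A margin of 2, borrowed from the planning effect, should not be adopted by default, since it would still pass about 28% of trials with a true risk ratio of 1.5.

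Cost: wording in two sections and one margin to justify. The rewording needs no extra patients. A stricter margin with adequate power would: for a margin of 1.5 at 80% power, (1.96 + 0.8416)² × 2 × (0.85/0.15) / (ln 1.5)² = about 541 per arm. The downside is that a null result may have to be reported as inconclusive.
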